# Assessing the efficacy of two dual-active ingredients long-lasting insecticidal nets for the control of malaria transmitted by pyrethroid-resistant vectors in Benin: study protocol for a three-arm, single-blinded, parallel, cluster-randomized controlled trial

**DOI:** 10.1186/s12879-021-05879-1

**Published:** 2021-02-19

**Keywords:** Dual-active ingredient long-lasting insecticidal nets, Chlorfenapyr, pyriproxyfen, Royal Guard®, Interceptor® G2, Malaria case incidence, Malaria prevalence, Entomological inoculation rate, Cluster randomized controlled trial, Benin

## Abstract

**Background:**

Long-lasting insecticidal nets (LLINs) are currently the primary method of malaria control in sub-Saharan Africa and have contributed to a significant reduction in malaria burden over the past 15 years. However, this progress is threatened by the wide-scale selection of insecticide-resistant malaria vectors. It is, therefore, important to accelerate the generation of evidence for new classes of LLINs.

**Methods:**

This protocol presents a three-arm superiority, single-blinded, cluster randomized controlled trial to evaluate the impact of 2 novel dual-active ingredient LLINs on epidemiological and entomological outcomes in Benin, a malaria-endemic area with highly pyrethroid-resistant vector populations. The study arms consist of (i) Royal Guard® LLIN, a net combining a pyrethroid (alpha-cypermethrin) plus an insect growth regulator (pyriproxyfen), which in the adult female is known to disrupt reproduction and egg fertility; (ii) Interceptor G2® LLIN, a net incorporating two adulticides (alpha-cypermethrin and chlorfenapyr) with different modes of action; and (iii) the control arm, Interceptor® LLIN, a pyrethroid (alpha-cypermethrin) only LLIN. In all arms, one net for every 2 people will be distributed to each household. Sixty clusters were identified and randomised 1:1:1 to each study arm. The primary outcome is malaria case incidence measured over 24 months through active case detection in a cohort of 25 children aged 6 months to 10 years, randomly selected from each cluster. Secondary outcomes include 1) malaria infection prevalence (all ages) and prevalence of moderate to severe anaemia in children under 5 years old, measured at 6 and 18 months post-intervention; 2) entomological indices measured every 3 months using human landing catches over 24 months. Insecticide resistance intensity will also be monitored over the study period.

**Discussion:**

This study is the second cluster randomised controlled trial to evaluate the efficacy of these next-generation LLINs to control malaria transmitted by insecticide-resistant mosquitoes. The results of this study will form part of the WHO evidence-based review to support potential public health recommendations of these nets and shape malaria control strategies of sub-Saharan Africa for the next decade.

**Trial registration:**

ClinicalTrials.gov, NCT03931473, registered on 30 April 2019.

**Supplementary Information:**

The online version contains supplementary material available at 10.1186/s12879-021-05879-1.

## Background

Insecticide-treated nets (ITNs) and, more recently, long-lasting insecticidal nets (LLINs) are the most widely used preventive measure for controlling malaria in sub-Saharan Africa (SSA) [1]. The World Health Organization (WHO) estimates that over 50% of the SSA population now sleep under LLINs and together with improved diagnosis and treatment, nets have contributed to an estimated 42 and 66% reduction in malaria incidence and mortality, respectively, over the last 15 years [2]. Pyrethroids are currently the only type of insecticide used routinely on LLINs, and the rapid spread of pyrethroid-resistant vectors seriously threatens to reverse the gains achieved so far [3]. Indeed, several studies have demonstrated that LLINs are becoming less effective at killing mosquitoes in areas of high resistance compared to areas of susceptibility [4, 5], although epidemiological evidence remains inconclusive in some studies [6, 7].

Due to concerns about the potential failure of current control tools as a result of insecticide resistance, WHO has encouraged manufacturers to develop new types of LLINs as part of the Global Plan for Insecticide Resistance Management in malaria vectors (GPRIM) [8]. The first nets to contain a mixture of active ingredients with evidence for impact on epidemiological outcomes were nets that combined a pyrethroid insecticide with the synergist piperonyl butoxide (PBO) which restores susceptibility to pyrethroid by neutralising mixed-function oxidase function responsible for resistance in vectors [9, 10].

New classes of ITNs combining two insecticides with differing modes of action could have the potential to improve vector control and delay the evolution of resistance and preserve the lifespan of both active ingredients (AI). The two most advanced products are the pyrethroid-pyriproxyfen LLIN (Olyset® Duo and Royal Guard®) [11–14] and a pyrethroid-chlorfenapyr LLIN (Interceptor® G2) [15–17]. Both types of LLINs have demonstrated improved efficacy in entomological studies but currently, limited epidemiological evidence has been generated. Most of the available evidence for these new nets are based on Phase I laboratory studies and Phase II experimental hut trials. Only Olyset® Duo has been tested in an randomized clinical trial (RCT) in Burkina Faso and demonstrated efficacy on malaria case reduction in comparison to clusters using standard pyrethroid nets [12].

There are currently no published data on the impact of Royal Guard® and Interceptor® G2 on malaria epidemiological outcomes. These LLINs need to be evaluated in the community to determine the full extent of their effectiveness for malaria control. Failure to do so will – as shown by the recent history of PBO LLINs [18, 19] – delay the scale-up of new and potentially effective tools due to lack of malaria control evidence. To receive a public health recommendation from WHO, new types of LLIN need to demonstrate improved epidemiological efficacy compared to standard pyrethroid LLIN in two settings [20]. A trial evaluating the same dual-AI LLINs is currently ongoing in Tanzania (clinical.gov, NCT03554616). West Africa constitutes a different environment and ecology from East Africa, with historically higher intensity of pyrethroid resistance in malaria vectors [21] and so far there is only limited entomological and epidemiological evidence that new mixture nets would have a better effect on malaria indicators compared to standard nets [14, 15].

The main objective of the present study is to assess the efficacy of two types of dual-AI LLINs on malaria in a setting where the main malaria vectors are resistant to pyrethroid insecticides. Secondary objectives are to assess the durability and bio-efficacy of the dual-AI LLINs in the community [22]; and to examine whether entomological outcomes from adapted experimental hut trials can predict epidemiological and transmission outcomes of the RCT using a malaria transmission model developed by Churcher et al. [23, 24]. The study protocol is reported in line with the Standard Protocol Items: Recommendations for Interventional Trials (SPIRIT) 2013 Statement [25].

## Study objectives

### Epidemiology

#### Primary objective

To evaluate the efficacy of two types of dual-AI LLINs compared to standard pyrethroid LLINs on malaria case incidence in children aged 6 months to 10 years during two years of follow up.

#### Secondary objectives

To assess the efficacy of each dual-AI LLIN compared to a standard pyrethroid-only LLIN on malaria infection prevalence in all age groups, and prevalence of moderate to severe anaemia in children under 5 years old, at 6 and 18 months post-net distribution.To assess if dual-AI LLINs have a safety profile similar to pyrethroid-only LLINs in the population of the trial study area.To monitor and evaluate the equity of study nets coverage and usage in the trial.

### Entomology

#### Primary objective

To assess the efficacy of each dual-AI LLINs compared to a standard pyrethroid-only LLIN on mosquito density, sporozoite rate, and the entomological inoculation rate (EIR) as a measure for malaria transmission.

#### Secondary objectives

To assess the impact of the new type of LLINs on *Anopheles* vector survivorship and other entomological outcomes (e.g., mosquito resting behaviour, species composition, feeding, ovary development, and fecundity).To assess annual changes in insecticide resistance intensity to the three insecticides used on the nets.

## Methods/design

### Study area

The study site is situated in Cove, Zagnanado, and Ouinhi Districts, located in the Zou department, central Benin, 154 km north of Cotonou, the economic capital (Fig. 1). The area was selected because of (i) a prevalence of malaria infection between 20 to 40%, (ii) high pyrethroid resistance in the main malaria vectors, (iii) and proximity to experimental hut sites. This area consists of 123 villages with approximately 54,000 households and population size of 220,000 inhabitants. The main economic activities of the population are farming, fishing, hunting, and trading [26, 27].

**Fig. 1 Fig1:**
[figure not shown]
Study area. Map showing Cove, Zagnanado and Ouinhi Districts, located in Zou department, central Benin, West Africa (Panel **a**); the 60 study clusters identified with core and buffer area and intervention allocation (Panel **b**); a minimum of 1000 m area was created between households in adjacent clusters (Panel **c**). Source of map: Own from the study investigators ([name]).

Malaria is highly endemic, and transmission occurs year-round. There are two rainy seasons, from April – July and from October – November. Malaria infection prevalence in the Zou department was 20% in children under 5 years old according to the demographic health survey (DHS) conducted in 2011–2012 [28] and increased to 36.5% in the 2017–2018 DHS [29]. The main vector control provision in the Zou department consists of the distribution of pyrethroid-only LLINs through regular universal coverage campaigns (most recently in 2017) and routine service delivery to pregnant women during antenatal care and to children under 5 years during extended programmes on immunization. According to the 2018 DHS, ITN usage in children under 5 years was 78.2%.

The main vector species are *Anopheles coluzzii* and *Anopheles gambiae* sensu stricto. Entomological surveys performed in the Cove region in 2015 revealed high levels of pyrethroid resistance intensity (> 200 fold) mainly due to high frequencies of kdr of > 90% and elevated cytochrome P450 enzymes [30].

### Trial design

The trial is a three-arm superiority, single-blinded, cluster-randomized trial with 20 clusters in each arm (60 clusters in total). The 3 arms are (i) mixture pyrethroid and chlorfenapyr LLIN: Interceptor® G2 (Intervention 1), (ii) mixture pyrethroid-pyriproxyfen LLIN: Royal Guard® (Intervention 2), (iii) pyrethroid-only standard LLIN: Interceptor® (Control/reference arm). The study design is summarized in Fig. 2.

**Fig. 2 Fig2:**
[figure not shown]
Summary of study design

Each cluster will be comprised of 1 village or a group of villages for an average of 200 households (1200 residents) per cluster. Clusters will have a minimum of 100 children and 100 households. A “fried egg” design will be used for cluster boundaries. Clusters will be designed with core and buffer areas to reduce the likelihood of spill-over of intervention effects. Nets will be distributed to all households in a cluster (i.e. core and buffer areas) but data collection to measure intervention effects will be restricted to households situated in the core areas to avoid spillover from neighbouring clusters receiving different nets. The cluster demarcation will be performed using the spatial analyst toolbox in ArcGIS (ESRI, Redlands, USA) based on the following criteria; a minimum of 50 children aged 6 months to 10 years in the core area and a buffer of minimum 1000 m between core households and any households in an adjacent cluster.

To estimate malaria case incidence, a cohort of 25 children per cluster aged 6 months to 9 years will be randomly selected from a census list of children living in the study clusters and followed over 24 months. For malaria infection prevalence assessment, two cross-sectional surveys will be conducted at 6 and 18 months post-net distribution; 70 individuals per cluster will be randomly selected for each cross-sectional survey, stratified by age (< 5 years, 5–9 years, 10–14 years, ≥15 years and older) from each of the 60 clusters.

Routine cross-sectional entomological surveys using human landing catches (HLCs) will be conducted in all clusters to assess the human biting rate and EIR. Each cluster will be visited once every three months. Four households will be selected from a census list in each study cluster at each time point. The first house will be randomly selected by the study data manager, while the other three will be chosen by the field team, in a radius of 15–20 m around the first one, to facilitate the supervision of mosquito collectors.

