### Interventions

#### Description of the study nets

The nets are blue, rectangular, and identical sizes (1.8 m long, 1.6 m wide, and 1.8 m high); however, the Royal Guard® textile is different from the other two nets (details below). The three net brands are all WHO pre-qualified vector control products [31].

Intervention 1: Interceptor® G2 (BASF Corporation) is a mixture LLIN made of polyester netting (100 deniers) coated with a wash-resistant formulation of 200 mg/m^2^ chlorfenapyr and 100 mg/m^2^ alpha-cypermethrin. Chlorfenapyr is a member of the pyrrole class of insecticides [32] and disrupts cellular respiration and oxidative phosphorylation in mitochondria and due to this unique mode of action is toxic to mosquitoes that are resistant to standard neurotoxic insecticides like pyrethroids [33]. No record of cross-resistance to chlorfenapyr has been reported up to now.

Intervention 2: Royal Guard® (Disease Control Technologies, LLC) is a mixture LLIN made of polyethylene (120 deniers) incorporating 225 mg/m^2^ pyriproxyfen and 261 mg/m^2^ alpha-cypermethrin. Pyriproxyfen is a multiple acting compound (known as a juvenile hormone analogue) with insecticidal and sterilising effects on females which is known to disrupt reproduction and fertility of eggs [34].

Control: Interceptor® LLIN (BASF Corporation) is a pyrethroid-treated LLIN with alpha-cypermethrin (coated onto filaments) at a target dose of 200 mg/m^2^ of polyester fabric (100 deniers). Interceptor was chosen as a direct comparison to Interceptor G2 and Royal Guard as all three nets are impregnated with alpha-cypermethrin pyrethroid (albeit at different concentrations) and because some pyrethroid resistance mechanisms involving CYP6 genes are specific to type I (permethrin) or type II (alpha-cypermethrin) pyrethroids [35].

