### Data collection, management, and analysis

#### Census

A short questionnaire will be used to collect demographic details on household residents to estimate the number of nets required to be distributed in each house and to randomly select children for the cohort. Each building will be mapped using a Global Positioning System to assist with delineating clusters.

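### Three of the four mosquito-collection houses per visit are neighbours picked by the field team with no selection rule: a local but avoidable route to selection bias in vector density and EIR

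*Protocol article*

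**What the plan says.** The entomology sampling is described under Trial design, in the text below Fig. 2. It opens with a general statement: "Four households will be selected from a census list in each study cluster at each time point". The procedure then splits. One house is a random draw made centrally by the data manager. For the rest, the text reads "while the other three will be chosen by the field team". Their choice is confined to a small circle, 15–20 m from the drawn house, and the reason given is easier supervision of the collectors. No rule is given for which houses inside that radius are used, or for what happens when the radius holds fewer than three others.

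Four other places bear on this:

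- **Census:** "Each building will be mapped using a Global Positioning System to assist with delineating clusters".
- **Description of the study nets:** the three nets share colour, shape and size, but the Royal Guard "textile is different from the other two nets". Royal Guard is 120-denier polyethylene. Interceptor G2 and Interceptor are both 100-denier polyester.
- **Assignment of interventions:** field staff are stated to be blinded to the allocation.
- **Secondary outcomes and the entomology objectives:** EIR is a secondary outcome, and mosquito density, sporozoite rate and EIR make up the primary entomology objective. Statistical methods estimates EIR per house per night.

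**The concern.** The opening sentence suggests that all four houses come off a list. The next shows that only one is drawn at random, and the other three depend on field staff judgement. The cohort children and cross-sectional participants described in the same section are randomly selected, so the entomology sample is the exception.

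Neighbouring houses can differ in wall and roof type, animals, number of sleepers and net use. Entomology activities has the team record these features, so the plan itself treats them as relevant. A team that prefers a welcoming or convenient house may therefore also be choosing on something related to biting density.

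If such choices are the same in all arms, the main loss is representativeness. If they differ by arm, the density and EIR contrasts are biased. Protection against the second case rests on blinding. One net is made of a different fabric, teams work inside houses, and each cluster is revisited every three months, so it is unwise to rely on blinding alone.

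**Working it through.** The plan states no sample size or precision for the entomological outcomes, so there is no figure of its own to reproduce. The check is a count, followed by an illustration of how selection would carry into an arm comparison.

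**Inputs**

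- Clusters: 60, that is 20 per arm (Trial design).
- Houses per visit: 4, of which 1 is random and 3 are team-chosen (Trial design).
- Visits: "Each cluster will be visited once every three months", giving 24 / 3 = 8 over the planned 24 months; 7 over 21 months after the COVID-19 amendment (Trial status).

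**Share of houses.** 3 / 4 = 75%.

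**House-nights** = clusters × houses × visits.

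| Plan | Total | Random | Team-chosen |
|---|---|---|---|
| Amended, 7 visits | 60 × 4 × 7 = 1,680 | 420 | 1,260 |
| Planned, 8 visits | 60 × 4 × 8 = 1,920 | 480 | 1,440 |

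Under the amended plan, each arm has 1,680 / 3 = 560 house-nights, of which 420 are team-chosen.

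**Reach of the discretion.** The choice is confined to a circle of area πr²: about 707 m² at 15 m and 1,257 m² at 20 m. The random first house sets where in the cluster that circle lies.

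**How selection would carry through (assumed values, not in the document).** Suppose team-chosen houses in an arm have a biting rate (1 + d) times that of randomly drawn houses, and all houses count equally. The arm mean is then multiplied by (1 + 3(1 + d)) / 4 = 1 + 0.75d.

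| d | Arm mean multiplied by | Shift if only that arm is affected |
|---|---|---|
| −0.10 | 0.925 | −7.5% |
| −0.20 | 0.850 | −15% |
| −0.30 | 0.775 | −22.5% |

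The rate ratio between two arms is multiplied by (1 + 0.75d₁) / (1 + 0.75d₀), where d₁ and d₀ are the values in the intervention and control arms. If d₁ = d₀ this equals 1 and the ratio is unchanged. For example, −0.20 in both arms gives 0.85 / 0.85 = 1. Non-random choice alone therefore does not bias the comparison; a difference in choice between arms does. The document offers no basis for a value of d or for such a difference.

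**Houses are not information.** Four houses within 20 m on one night are likely to be correlated. With an assumed within-spot correlation ρ, their effective number is 4 / (1 + 3ρ): 2.5 at ρ = 0.2 and 1.6 at ρ = 0.5. The 75% is a share of houses, not of mosquitoes or of statistical information.

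**The case against.** The strongest defence is that this is a disclosed field compromise with a stated reason, supervision of collectors, and that it resembles a random spot with its immediate neighbours. Several parts of that defence stand:

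- Teams cannot choose where in the cluster to work, and where few houses lie inside the radius they have little to choose from.
- All households in a cluster receive the same type of net, so choosing a neighbour cannot change the intervention.
- House type, animals and malaria prevention measures are recorded, and Statistical methods adjusts the density and EIR models for confounders found to be imbalanced. This helps, but it cannot reach unrecorded reasons for choosing a house.
- Collections had already resumed when the article was written, so a change now makes later rounds differ from earlier ones. That is a real cost, though a manageable one.

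A reader might infer something stronger: that three quarters of the entomology data come from unrestricted convenience sampling by staff who know the arm. The document does not support that. The radius ties every chosen house to a random one. Nothing says that staff recognise any net; it says only that one textile differs, and it states that field staff are blinded. The fabric argument also does not reach Interceptor G2 against Interceptor, since both are 100-denier polyester.

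**Conclusion.** The point holds as a design weakness of modest weight. For 75% of collection houses (1,260 of 1,680 house-nights over seven rounds), selection within a 15–20 m radius is left to the field team without a rule, which fits poorly with the statement that the houses come from a census list.

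Any resulting bias is probably limited, because the discretion is local. Its size cannot be derived from the document, and the 7.5% to 22.5% shifts above only illustrate assumed deviations in one arm. Bias between arms requires choices that differ by arm and relate to biting density. Possible recognition of the Royal Guard fabric makes that most plausible for Royal Guard against control, but recognition is an inference.

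The outcomes at risk are density and EIR. Malaria case incidence, the primary outcome, is unaffected, because cohort children are randomly selected from a census list. The case for acting is that the route is avoidable at small cost, not that bias has been shown.

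**What to change.** Before each remaining round, the data manager should pre-specify all four houses from the census and GPS building map:

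1. Draw the first house at random, as now.
2. Select the three neighbours by random draw among listed houses inside the supervision radius, or by a fixed rule such as the nearest listed houses.
3. Attach an ordered reserve list, and set in advance a fixed step by which the radius widens if it holds too few houses.
4. Allow the team to replace a house only in list order, logging each replacement and its reason.
5. Start the change in the same round in all arms and record that round, so that earlier and later rounds can be told apart in the analysis.

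This cuts the team-chosen share of planned selections from 75% to 0% in the rounds it covers, with the number of house-nights unchanged. It costs a few lines of sampling code, a revised operating procedure, an occasional slightly wider radius for the supervisor, and a documented change of selection method part-way through. It cannot repair rounds already collected.

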### Eligibility criteria

The cohort will include children aged 6 months to 9 years old resident in the study villages, without any severe illnesses and whose parents/carers have given written informed consent for their child to be included in the study. Inclusion criteria during cross-sectional surveys will be the willingness to participate and provide consent (or for parents/carers to provide consent for children); resident in the village during the previous 3 months, selected individuals without severe illness.

